### Summary of Work to Date

Our review of the medical records for 102 youth receiving specialist mental health support at CHEO found lifestyle counselling was included within mental health treatment for 95% of patients. In response, the expertise of 10 youth inpatients, 10 youth outpatients, 10 parents and 10 clinicians defined their desired type of lifestyle support. The HEalthy Lifestyle Project (HELP) resources were then iteratively and collaboratively designed with 12 inpatients, 33 outpatients, 18 parents, 11 clinicians and 23 Indigenous youth and elders (CHEO REB#20 62X).

Our pilot study of the HELP e-intervention enrolled youth contacting 1Call1Click or on the CHEO waitlist for specialist mental health services (CHEO REB#21 85X). 42% of youth waiting for specialist mental health support were eligible. Student researchers were able to approach 62% of eligible youth and successfully recruited 35% (n=10/29) in 4 months. Youth/families/clinicians requested the HELP pilot study be expanded to include youth seeking or receiving mental health support, adding new partners to our team (i.e., YouthNet/Réseau Ado, CHEO Youth Forum, 1Call1Click central intake). 26% (6/23) of teens enrolled in the next four months, with 5/6 youth having complete data. Most who expressed interest but did not enroll found the study questionnaires daunting as they were required to complete them virtually without researcher support. 83% (5/6) of enrolled youth demonstrated good engagement and measurable improvements in emotional health and lifestyle behaviours aligned with resource use. HELP resource engagement improved **
[figure not shown]
**sleep scores by 13%, decreased screen time by 0.96 hours/day and increased physical activity by 26 minutes/day. These changes allowed youth to achieve the recommended sleep and physical activity behaviours and reduce excessive screen use by approximately 50%.

Legend: Positive change was lower score for Strengths and Difficulties Questionnaire.

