### Study Rationale

Lifestyle behaviour change through intensive in-person support has a positive impact on mental health. However, the youth mental health crisis creates a clear need to identify novel, scalable lifestyle behaviour change supports that can meet high demand. HELP is not an education intervention, but a novel virtual, asynchronous and scalable step-by-step support for self-guided lifestyle behaviour change. Youth anxiety/depression scores improved in 16 exercise RCTs^24^. 73 youth studies found improved psychological distress, anxiety, depression, and emotional disturbance linked to physical activity^25^. Decreasing recreational screen time, particularly phone/tablet use, improved adolescent mental health^26^. Sleep difficulties both determine and result from of youth mental health issues^27^. Targeting youth insomnia (6 weekly sessions) significantly improved psychological distress. These studies provide clear evidence of the mental health🡪lifestyle behaviour link^5,25,28–30^ and the impact of lifestyle behaviours on emotional health.

Knowing that only 17.5% of Canadian youth meet sleep, physical activity and screen time guidelines^31^, our team collaboratively developed the interactive HEalthy Lifestyle Project (HELP) e-intervention modules. HELP implements an innovative mental health care model that targets the important gap in timely youth mental health care. HELP is designed to engage youth in a step-by-step behaviour change journey focused on decreasing screen time, increasing physical activity, and/or improving sleep. We hypothesize that immediate access to the HELP intervention will support both prevention and treatment; reducing disease burden and long conventional therapy wait times^32^. The youth-initiated HELP format provides many youth-focused benefits^33^ and shares our lived experience of youth mental illness and mental health care, lifestyle behaviour change, and e-health expertise. Lifestyle e-interventions are stigma-free, have few side effects, can be done alone or with family and enable self-help strategies^14^. They also offer easy access, greater reach, flexibility for individual needs, and relatively lower cost.

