### Research Questions

1. Do youth (12 to 17 years of age) who engage in the 6-month HELP e-intervention have a larger improvement in emotional health (measured by the Strengths and Difficulties Questionnaire) than youth who do not receive the intervention?
2. Does engagement in the HELP e-intervention improve lifestyle behaviour (physical activity, sleep or screen time)?
3. Are changes in emotional health and lifestyle behaviours sustained for at least 6 months after completion of the HELP e-intervention?
4. Do youth who engage in the 6-month HELP e-intervention utilize fewer mental healthcare resources, during and for 1 year following RCT participation, than youth who do not receive the intervention?
5. Do mental health professionals supporting youth who engage in the 6-month HELP e-intervention provide lifestyle behaviour support less frequently than for youth who do not receive the intervention?
6. Are self-reported (i.e., perceived) lifestyle behaviour changes (study questionnaire responses) aligned with objective measures of screen time (smartphone tracking) and sleep and physical activity (accelerometry) in a randomly selected sub-sample (1 of 3) enrolled participants?

We hypothesize that youth engaging in the HELP e-intervention will have improved emotional health and enhanced lifestyle behaviours in comparison to those receiving the delayed (post 6-months) intervention. We hypothesize that changes during the intervention will be maintained for an additional 6 months, and that self-reported measures will accurately reflect objective measurements. We hypothesize that youth engaging in the HELP e-intervention will require fewer youth mental health supports, and when supported will be less likely to require treatment directed at lifestyle behaviours.

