## Expected Duration of Participation

Youth will participate in the study for 12 months. All study visits and assessments are completed remotely. Youth can choose to complete the assessments via RedCAP survey or to have paper copies of the questionnaires sent by mail. The research coordinator will work virtually with each participant to support questionnaire completion. Completion of all questionnaires will require approximately 1 hour at each assessment timepoint. One of every three participants will be randomly selected to complete the objective behaviour measurements in addition to the questionnaires. Accelerometers will be distributed and collected by mail so that in-person visits to CHEO are not required. Participants selected for the objective measures will be required to wear an accelerometer on an elastic waistband 24 hours per day for 7 consecutive days. They will also be required to submit a screen shot of their social media screen time (app that already exists in smartphones) daily for the same 7 days. After the four assessment timepoints have been completed, youth will no longer be required to perform study activities but data collection on healthcare system impacts will continue to be collected via medical chart review for an additional 6 months. Participants randomized to the wait list control group will have access to the HELP e-intervention between the 6 and 12-month assessment timepoints.

| **Study Group** | **0 mos** | **0 to 3 mos** | **3 mos** | **3 to 6 mos** | **6 mos** | **6 to 12 mos** | **12 mos** | **12 to 18 mos** |
| --- | --- | --- | --- | --- | --- | --- | --- | --- |
| Intervention | Assess | HELP | Assess | HELP | Assess | ----- | Assess | Medical chart |
| Wait List Control | Assess | ----- | Assess | ----- | Assess | HELP | Assess | Medical chart |

Assess = completion of study questionnaires and objective measures (if applicable)
HELP = access to the HELP e-intervention with kinesiologist support
Medical chart = evaluation of mental health service use and inclusion of lifestyle behaviours in mental health service supports via medical chart review for 18 months from study enrollment

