The blinded researcher will also administer the objective measures of sleep, physical activity and lifestyle to a randomly selected sub-sample of participants. One in every three participants will be provided by mail with an accelerometer to wear for 7 days at the time of the 0 and 6-month assessments. Each selected youth will wear a tri-axial accelerometer (Actigraph GT9X-BT, 180 day memory) on a waist-worn belt, over the right hip, in the mid axillary line, 24 hours/day for 7 days^40^ in addition to completing the study questionnaires. The goal is 24 hour accelerometer wear for 7 consecutive days to capture both physical activity and sleep, and to minimize data loss (monitor forgotten, etc.). The Actigraph GT9X-BT ([www.theactigraph.com](http://www.theactigraph.com)) can be worn for swimming or bathing to a 1-metre depth. Sleep times and reasons for device removal will be recorded on a log sheet (Appendix G). A minimum of 10 hours of wear time per day during waking hours will be required so that established cut points^41^ can be used to calculate daily minutes of sedentary, light and moderate+vigorous activity. The ActiLife software (Version 6.13.5, Actigraph Inc.) also calculates sleep duration based on measurement epochs lacking movement. At least 3 weekdays and 1 weekend day of valid data will be required. Screen use will be measured by utilizing the social media tracking function in the smartphone owned by each participant^42^. The researcher will explain to each participant how to access the social media tracking function that is build into their smartphone. Participants will be asked to take a screen shot of their social media use each day at the time they go to bed and to share the screen shot with the research team. Participants who do not own a smartphone will not complete the objective measures of lifestyle behaviours.

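### The daily phone screenshot is tied to bedtime with no rule for which calendar day it must show, so nights that end after midnight may be under-recorded and the measured change in screen use biased

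*Protocol*

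**What the plan says.** Study Assessments names the instrument: "Screen use will be measured by utilizing the social media tracking function in the smartphone owned by each participant". The same section sets the time of capture: "Participants will be asked to take a screen shot of their social media use each day at the time they go to bed". Expected Duration of Participation adds only that selected youth "submit a screen shot of their social media screen time (app that already exists in smartphones) daily for the same 7 days".

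Neither section gives a clock time, a day boundary, an instruction to show the previous day, or a rule for bedtimes after midnight. The protocol does not say when the tracker resets or whether earlier days stay viewable.

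The accelerometer is worn "to wear for 7 days at the time of the 0 and 6-month assessments", and the screenshots cover the same week. The measure is for a subsample: "One of every three participants will be randomly selected to complete the objective behaviour measurements in addition to the questionnaires". It serves research question 6, which asks whether self-reported lifestyle changes are "aligned with objective measures of screen time (smartphone tracking) and sleep and physical activity (accelerometry").

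The intervention is "focused on decreasing screen time, increasing physical activity, and/or improving sleep" (Study Rationale). Study Assessments also has sleep times entered on a log sheet during the accelerometer week, but does not link that log to the screenshots.

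**The concern.** A daily total is only usable if it covers a whole, identifiable day. A screenshot taken at 22:30 shows nearly all of the day. One taken at 00:30 on a tracker that counts by calendar day shows half an hour of the next day, and nothing in the protocol stops it being filed as the day just ended. Any use between the screenshot and midnight, for instance in bed, is missed too.

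This would matter less if the error were stable. It depends on bedtime, and HELP has a sleep component, so the error could differ between month 0 and month 6. If some bedtimes move from after to before midnight, recorded use rises on those nights for a reason unrelated to screen use, and a real reduction is masked in part. If bedtimes move later, a reduction is exaggerated. Either way, accurate self-report could be judged to disagree with the objective measure, which is the conclusion research question 6 is meant to test.

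This is separate from whether social media use stands in well for all leisure screen time. It would arise even if the two measures covered the same content.

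**Working it through.** The protocol gives no figure on this point, so there is nothing to reproduce. The two models below size the effect. Both assume that the tracker restarts at 00:00 and that the screenshot shows the current day.

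**Model A: level of under-recording**

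Assumed inputs, none from the protocol: true use 180 min/day; half of the minutes between midnight and bedtime spent on social media; bedtimes normally distributed, mean 23:00 on weekdays and 24:00 on weekends, SD 45 or 60 min; nights weighted 5:2.

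Recorded mean = 180 × (1 − p) + 0.5 × E. Here p is the share of nights with bedtime after midnight, and E is the mean number of minutes past midnight, counted as zero on nights that end earlier.

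- SD 45 min: weekday p = 1 − Φ(60/45) = 0.091; weekend p = 0.5. Weighted p = (5 × 0.091 + 2 × 0.5)/7 = 0.208. E = 6.5 min. Recorded = 142.6 + 3.2 = 145.8 min. Shortfall = 34.2/180 = 19%.
- SD 60 min: weekday p = 1 − Φ(1) = 0.159. Weighted p = (5 × 0.159 + 2 × 0.5)/7 = 0.256. E = 10.4 min. Recorded = 133.9 + 5.2 = 139.1 min. Shortfall = 40.9/180 = 23%.

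| Assumed mean bedtime (weekday/weekend) | Recorded mean, true 180 min | Shortfall |
| --- | --- | --- |
| No bedtime after midnight | 180 | 0% |
| 22:30 / 23:30 | 158-165 | 8%-12% |
| 23:00 / 24:00 | 139-146 | 19%-23% |
| 23:30 / 00:30 | 115-117 | 35%-36% |

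If every bedtime moved from the third row to the second (30 min earlier) with no change in use, recorded use would rise from 145.8 to 165.2 min or from 139.1 to 157.9 min. That is about 19 min/day, or 13%.

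Model A leaves out after-midnight minutes that reappear in the next day's total. Model B counts them.

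**Model B: change from month 0 to month 6**

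H = hours used before midnight, u = hours used after midnight on late nights, p = share of late nights, independent between nights.

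- True mean = H + p·u
- Recorded mean = (1 − p)(H + p·u) + p·u

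Take H = 4 h at month 0 and 3.04 h at month 6, a fall of 0.96 h/day (a reduction of the size the pilot reported), and u from 0.25 to 1 h. For p falling from 0.3 to 0.1:

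- u = 0.25: recorded 0.7 × 4.075 + 0.075 = 2.93 h, then 0.9 × 3.065 + 0.025 = 2.78 h. Recorded change −0.14 h; true change −1.01 h.
- u = 1: recorded 0.7 × 4.30 + 0.30 = 3.31 h, then 0.9 × 3.14 + 0.10 = 2.93 h. Recorded change −0.38 h; true change −1.16 h.

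| Late-night share, month 0 to month 6 | True change (h/day) | Recorded change (h/day) |
| --- | --- | --- |
| 0 to 0 | −0.96 | −0.96 |
| 0.1 to 0.05 | −0.97 to −1.01 | −0.74 to −0.80 |
| 0.3 to 0.1 | −1.01 to −1.16 | −0.14 to −0.38 |
| 0.5 to 0.2 | −1.04 to −1.26 | +0.04 to +0.33 |

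With H between 2 and 6 h at month 0, the 0.3 to 0.1 shift gives a recorded change from −0.78 to +0.26 h. The usual result is a reduction that looks too small. The sign reverses only when the shift across midnight is large or daily use is high.

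**How many are measured**

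One third of the 122 complete cases in Sample Size Determination is about 41 youth. One third of 100-200 enrolled is 33-67.

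**The case against.** The strongest reply is that the protocol never tells youth to submit the new day's total. It asks for each day's use, and the researcher will explain how to reach the tracking function, so the participant instructions could settle which day to show. That is fair as far as it goes. Still, the one timing rule the protocol fixes is bedtime, and a youth who follows it after midnight is given no reason to look back a day.

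Several stronger readings are tempting and do not hold:

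- **That a late night's data are lost.** A reader might infer this, but the protocol does not describe the tracker's reset or its history. If earlier days stay viewable, the total can be recovered, and the proposed fix relies on that.
- **That HELP will make screen use appear to rise.** The protocol names better sleep as an aim, not earlier bedtimes, and reports no bedtimes and no bedtime effect. Youth may also work on only one of the three behaviours. A shift that does not cross midnight does not cause this bias.
- **That the artefact is a known fraction of the pilot effect.** The pilot reported "decreased screen time by 0.96 hours/day and increased physical activity by 26 minutes/day", but the protocol does not say that this came from phone tracking. Setting social media minutes against it would mix two measures. Model B borrows 0.96 h only as a plausible size of reduction.
- **That the sizes are estimates.** They rest on assumed inputs. The 24:00 weekend mean alone puts half of weekend nights past midnight, which supplies 2 × 0.5/7 = 14.3 of the 21-26 percentage points of late nights in the 23:00/24:00 case.

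The sleep log is a partial safeguard, since late nights could be identified from it. No rule says that it will be used for this.

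**Conclusion.** The point holds as a gap in the capture rule. The screenshot is tied to bedtime, and the protocol does not say which calendar day it must show. If the total restarts at midnight and the current-day view is captured, late nights are under-recorded: about 19%-23% on average under the 23:00/24:00 assumption, 8%-36% across the three bedtime scenarios, and nil if no bedtime is after midnight. A shift of bedtimes across midnight between months 0 and 6 biases the measured change; if the shift is to earlier bedtimes, a true reduction usually looks smaller. Whether such a shift will occur cannot be told from the protocol.

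The reach is narrow: the screen-time part of research question 6, in the one-in-three subsample. The SDQ primary outcome and the questionnaire measure of screen time are untouched. The change is still worth making, because it is nearly free and later analysis cannot restore a daily total that was never captured.

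**What to change.** In Study Assessments and the participant instructions, replace the bedtime screenshot with one taken each morning that shows the previous calendar day's completed total, for each of the 7 days. Where the phone displays them, the seven daily totals could instead be captured once the week has ended. Use these full-day totals in the research question 6 comparison at months 0 and 6. Under both models the midnight bias is then zero at any bedtime, and use after going to bed is counted.

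For any screenshots already taken at bedtime, use the sleep log to flag nights with bedtime after midnight, and state how flagged nights are handled.

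The cost is one sentence in the protocol and in the instructions. Daily morning capture needs the same number of screenshots and no added staff or equipment. The downside is that youth must look back one day, so confirm beforehand that each participant's phone shows the previous day's total.

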### Study Assessments

A researcher blinded to study group allocation will work with enrolled youth to complete all study assessments. The accurate/reliable study questionnaires include measures of emotional strength (Strengths and Difficulties Questionnaire)^34^, lifestyle choices (Youth Quality of Life-short form)^35^, readiness for behaviour change (Stages of Change Questionnaire^36^), and sleep (Adolescent Sleep Hygiene Scale)^37^, physical activity (Habitual Activity Estimation Scale)^38^, and leisure screen time (Adolescent Sedentary Activity Questionnaire)^39^ behaviours. All enrolled youth will complete all questionnaires at 0, 3, 6 and 12 months. As in our pilot study (REB #21 85X), the questionnaires (Appendix E) will be completed virtually using RedCAP, with automated scoring of the responses according to published methods. At each assessment, youth will be asked to voluntarily self-report age (years), gender (boy, girl, unkown, other, prefer not to answer), and their use of other mental health therapies (Appendix F). Study enrollment does not restrict access to or use of other mental health supports.

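### The screen-time part of research question 6 compares leisure screen time by questionnaire with smartphone social media use by screen shot, so the result cannot show whether self-report is accurate

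*Protocol*

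**What the plan says.** In Research Questions, question 6 reads in part: "Are self-reported (i.e., perceived) lifestyle behaviour changes (study questionnaire responses) aligned with objective measures of screen time (smartphone tracking". It applies to a random one-in-three sub-sample. The hypothesis in the same section is that "self-reported measures will accurately reflect objective measurements".

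The self-report side is described in Study Assessments as "leisure screen time (Adolescent Sedentary Activity Questionnaire", and Study data describes it in the same way. Neither section limits the questionnaire to a device or an application.

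The objective side is narrower. Study Assessments says: "Screen use will be measured by utilizing the social media tracking function in the smartphone owned by each participant". On timing it adds: "Participants will be asked to take a screen shot of their social media use each day at the time they go to bed". Expected Duration of Participation confirms the content, since selected youth must "submit a screen shot of their social media screen time (app that already exists in smartphones) daily for the same 7 days".

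Study Rationale treats phone and tablet use as one part of recreational screen time: "Decreasing recreational screen time, particularly phone/tablet use, improved adolescent mental health". No section says how the questionnaire score and the phone record would be made comparable, or how use after the screen shot is counted.

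**The concern.** Question 6 is a validity check on self-report. Such a check needs the same quantity on both sides, so that any gap can be read as reporting error. Here the phone record covers one kind of use on one device up to one moment of the day, while the questionnaire asks about leisure screen time without that limit. A youth who reduces leisure screen use elsewhere could report this truthfully and show no change on the phone.

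The inference fails in both directions. A weak association would not show that self-report is inaccurate, and a strong one would not validate self-reported leisure screen time. The hypothesis about self-report accuracy could not be cleanly interpreted for one of the three behaviours that HELP targets.

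The problem lies in what is collected. A later analysis plan cannot recover phone use that was never recorded.

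**Working it through.** The protocol gives no sample size, agreement index or threshold for question 6, so there is no stated figure to reproduce. The check is what perfect self-report would look like against the phone record.

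**Inputs**
- Self-report quantity: leisure screen time (Study Assessments, Study data).
- Objective quantity: social media use on the participant's own smartphone, captured at bedtime (Study Assessments, Expected Duration of Participation).
- Target of question 6: change. Study Assessments places the accelerometer weeks at 0 and 6 months, and the screen shots cover the same 7 days, so a change can be formed.
- Pilot change in screen time, for illustration only: a fall of 0.96 hours/day (Summary of Work to Date).
- Share of leisure screen time that is smartphone social media: not in the documents. Assumed ranges are used below.

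**Set-up.** Let S be smartphone social media use, O all other leisure screen use, and T = S + O the error-free self-report. The phone records S. Use after the screen shot is ignored here because nothing in the protocol sizes it.

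**Levels.** The phone recovers the share f = mean(S)/mean(T). At f = 25%, 50% or 75% it falls short of perfect self-report by 75%, 50% or 25%. The two agree only at f = 100%.

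**Changes.** Write dS, dO and dT for the 0-to-6-month changes, v = var(dS)/(var(dS) + var(dO)), and r = corr(dS, dO). Then

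corr(dT, dS) = (v + r·√(v(1−v))) / (√v · √(1 + 2r·√(v(1−v)))).

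1. Other screen use unchanged (dO = 0): dT = dS, so the changes agree exactly.
2. Both components change in a fixed proportion: the correlation is 1.00, but the phone shows only the fraction f of the change. With the pilot figure, 0.96 × 0.25 = 0.24, 0.96 × 0.50 = 0.48 and 0.96 × 0.75 = 0.72 hours/day.
3. Components change independently (r = 0): the formula reduces to √v. Lin's concordance, with no mean shift, is 2v/(1 + v).
4. Other screen use partly replaces social media (r = −0.5). For example, at v = 0.5, √(v(1−v)) = 0.5, the numerator is 0.5 − 0.25 = 0.25, the denominator is √0.5 × √0.5 = 0.5, and the correlation is 0.50.

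| v | correlation, r = 0 | concordance, r = 0 | correlation, r = −0.5 |
|---|---|---|---|
| 0.8 | 0.89 | 0.89 | 0.87 |
| 0.5 | 0.71 | 0.67 | 0.50 |
| 0.2 | 0.45 | 0.33 | 0.00 |

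Self-report is perfect in every row. The spread from exact agreement to zero correlation therefore comes only from how youth divide their screen use, which the planned data do not observe.

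**The case against.** The best case for the plan is that question 6 asks about change, and changes in a part can track changes in the whole. Cases 1 and 2 above show this: agreement can be exact, or the correlation can be 1.00. That stands. A reader might infer that the comparison must show misalignment even with perfect self-report. For changes the documents do not support that, and misalignment is only possible. For levels it follows unless smartphone social media is all of a youth's leisure screen time. Nor are 0.89, 0.71 and 0.45 general ceilings. They hold under assumed independence, and positively related changes give higher values.

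Three further limits also stand.
- A reader might take the questionnaire to cover television, gaming and every other device. Its items are in an appendix that is not shown, so the mismatch has to rest on the two descriptions in the text.
- A reader might infer that HELP targets phone use at bedtime. HELP E-Intervention lists Screen Time and Sleep sections but does not mention that behaviour.
- The protocol does not say that a discrepancy will be put down to reporting bias. The choice of index and of questionnaire items may properly sit in an analysis plan.

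That last argument does not rescue the comparison. An analysis plan could select matching questionnaire items if they exist, but it cannot widen a phone record that holds only social media use.

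The stakes are also limited: one of three behaviours, in the last of six questions, in a one-in-three sub-sample.

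**Conclusion.** The point holds as a mismatch of measured quantities. As written, the screen-time part of question 6 cannot separate reporting error from the difference between leisure screen time and smartphone social media use, and good agreement would not validate the former.

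The size is not fixed by the documents. With error-free self-report it runs from no discrepancy, through the independent-change correlations in the table, to lower values under substitution. These figures rest on assumed variance shares of 20% to 80% and on the assumed relation between components. The loss after the bedtime screen shot adds to the gap by an amount that cannot be sized.

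The primary outcome (Strengths and Difficulties Questionnaire) and the sleep and physical activity comparisons are not affected.

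**What to change.** Before objective data are collected, put the same quantity on both sides, in one of two ways.

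- **(a) Narrow the question.** Restrict the screen-time part of question 6 and its hypothesis to smartphone social media use, and compare the screen shots with a self-report item on that same use. This is the cheaper option.
- **(b) Widen the phone record.** Have selected youth submit the phone's total screen time, by category rather than by app, for each completed previous day. Compare it only with the questionnaire's phone items, if such items exist. Reporting on completed days also removes the loss after bedtime.

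Under (a), state how use after the screen shot is counted. Under either option, do not claim validation of total leisure screen time.

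The cost is a change to the participant instruction, an ethics amendment and a sentence on the comparison, plus one added item under (a) if none exists. The number of screen shots need not rise. Option (b) collects slightly more personal data from 12-17-year-olds, its totals include non-leisure phone use, and other screens remain unmeasured.

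### As worded, the smartphone rule also keeps selected youth without a phone out of accelerometry, so the objective sleep and activity data would come from smartphone owners only

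*Protocol*

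**What the plan says.** Research question 6 (Research Questions) asks whether self-reported behaviour change agrees with "objective measures of screen time (smartphone tracking) and sleep and physical activity (accelerometry) in a randomly selected sub-sample (1 of 3) enrolled participants". Each behaviour therefore has its own instrument, and the sample is to be a random third of those enrolled.

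Study Assessments describes the two instruments separately:

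- **Accelerometer (sleep, physical activity).** "One in every three participants will be provided by mail with an accelerometer to wear for 7 days". The device has a 180-day memory and is accompanied by a paper log of sleep times and removals. Expected Duration of Participation adds: "Accelerometers will be distributed and collected by mail so that in-person visits to CHEO are not required".
- **Phone (screen time).** "Screen use will be measured by utilizing the social media tracking function in the smartphone owned by each participant", with a daily screen shot sent to the research team.

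The paragraph then closes with the rule at issue: "Participants who do not own a smartphone will not complete the objective measures of lifestyle behaviours". It makes no exception for the accelerometer and gives no reason.

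Owning a smartphone is not among the Inclusion Criteria. Youth must only be willing to do the objective measures if selected, so youth without a phone can enrol and can be selected.

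**The concern.** The rule ties two unrelated instruments together. A youth with no phone cannot supply screen shots, but nothing described for the accelerometer depends on having one. Applied literally, the rule stops staff mailing an accelerometer to a selected youth who could have worn it.

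Two things follow for research question 6. First, the sleep and activity comparison would be made in smartphone owners, although the question promises "in a randomly selected sub-sample (1 of 3) enrolled participants". Second, this is a rule of data collection: accelerometer weeks that were never recorded cannot be restored by any later analysis. That makes the sentence worth settling before recruitment, even though the sub-study is a small part of the trial.

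**Working it through.** The Protocol gives no smartphone ownership rate and no sample size for research question 6, so there is no stated figure to reproduce. The check is first a reading of the text, then a scale calculation on assumed rates.

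**1. What the rule covers**

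- Research question 2 reads "Does engagement in the HELP e-intervention improve lifestyle behaviour (physical activity, sleep or screen time", so its parenthesis gives the term three components.
- Potential Benefits to Participants credits hours for the objective lifestyle measurements as one package, without separating the accelerometer from the screen shots.
- With that usage, the rule covers all three objective measures.

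**2. What needs a phone**

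| Behaviour | Instrument | Phone step described? |
|---|---|---|
| Sleep | Mailed accelerometer plus log | No |
| Physical activity | Mailed accelerometer plus log | No |
| Screen time | Tracking function on the youth's own phone | Yes |

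The rule is needed for one row and, as worded, applies to three.

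**3. How many youth**

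Inputs: expected enrolment of about 100-200 and the figure of 122 (both from Sample Size Determination; 122 is the number with complete data in the power statement, used here only for scale); selection of 1 in 3; an **assumed** share q without a phone; **assumed** no replacement of selected non-owners.

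Formula: loss = (N / 3) × q.

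| N | N / 3 | q = 5% | q = 10% | q = 15% |
|---|---|---|---|---|
| 100 | 33.3 | 1.7 | 3.3 | 5.0 |
| 122 | 40.7 | 2.0 | 4.1 | 6.1 |
| 200 | 66.7 | 3.3 | 6.7 | 10.0 |

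Over a wider assumed range of 2-20%, the loss runs from 33.3 × 0.02 = 0.7 to 66.7 × 0.20 = 13.3 youth.

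**4. Effect on precision**

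Take an assumed correlation of r = 0.5 between self-report and accelerometer, with 95% limits tanh(atanh(r) ± 1.96/√(n − 3)) and atanh(0.5) = 0.549.

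- n = 41: 1.96/√38 = 0.318, giving 0.23 to 0.70.
- 10% lost, n = 36.9: 1.96/√33.9 = 0.337, giving 0.21 to 0.71.
- 20% lost, n = 32.8: 1.96/√29.8 = 0.359, giving 0.19 to 0.72.

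**5. Effect of the narrower population**

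If mean reporting error differed by D standard deviations between youth with and without a phone, the mean in owners would differ from the mean in all selected youth by q × D. With q = 10% and D = 0.5, that is 0.05 SD; with q = 20% and D = 0.8, it is 0.16 SD. Both inputs are assumptions. The Protocol has no data on D, and D may be zero.

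**The case against.** **The sentence may mean screen use only.** The paragraph opens by listing lifestyle as a third item beside sleep and physical activity, which fits screen use, and the rule comes directly after the screen-shot instructions. On that reading nobody loses the accelerometer. The usage in Research Questions and in Potential Benefits to Participants points the other way, so the wider reading is the more natural one, but it is not certain. What stands is that the sentence is at least unclear, and staff following it literally would withhold the device.

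**There may be a reason.** Having all three measures on the same youth, with one denominator, is a sensible aim. A reader might infer that the exclusion is arbitrary; the Protocol shows only that no reason is stated.

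**No bias is shown.** A reader might infer that the rule removes the youth whose habits differ most and so distorts the validation. The Protocol contains nothing on the sleep, activity, age, family means or reporting accuracy of youth without a phone. The comparison would be distorted only if reporting accuracy varied with ownership. Otherwise the rule merely narrows the population described. This objection stands in full.

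**The loss may be nil.** The Protocol does not say whether a selected non-owner is replaced, or whether selection is made among owners. Either would keep the sub-sample at its planned size. The counts above therefore hold only without replacement. Replacement would not answer the point about who is represented.

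**Conclusion.** The point holds in a limited form. As worded, the rule bars selected youth without a smartphone from accelerometry that needs no phone. This conflicts with the stated random third of enrolled participants, because owning a phone is not an entry condition. If only screen use was meant, the sentence fails to say so. Either way it needs the same correction.

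The size is unknown and probably small: about 2-6 of 41 youth if 5-15% lack a phone and none is replaced. The confidence interval for agreement hardly moves. Only research question 6 is affected; the primary Strengths and Difficulties Questionnaire outcome and the questionnaire-based outcomes are untouched. The documents do not support a claim that the validation result would be biased. This is a low-cost improvement, not a threat to the trial.

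**What to change.** In Study Assessments, replace the rule with wording such as: *A selected youth without a smartphone completes the accelerometer measures and omits only the smartphone screen-time measure.* Report how many selected youth this applies to. If the investigators do want all three measures on the same youth, they should state that reason and describe the sub-sample as drawn from smartphone owners.

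The cost is one sentence. Accelerometers are already planned for one participant in three, and no new instrument or procedure is added. There is a small downside: the accelerometry and screen-time analyses will have slightly different denominators, and any joint analysis of all three measures remains limited to owners. The change recovers sleep and activity data only; it cannot supply objective screen-time data for youth without a phone.
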